**FIGURE 1 F1:**
[figure not shown]
Trial flowchart.

### Sample size

Sample size calculation: The sample size was estimated using G*Power software, incorporating considerations for cognitive and fMRI outcomes. Adjustments were made to account for dropout rates, multiple comparisons, and desired statistical power.

For cognitive outcomes, the required sample size was calculated based on an effect size of, derived from previous studies evaluating Tai Chi interventions in older adults with MCI (Bossers et al., 2015). Similar studies report comparable effect sizes regarding improvements in cognitive function (Guo et al., 2024). To achieve 95% power at a significance level, a total of 56 participants are required. Accounting for an anticipated dropout rate of 35% (Dignan et al., 2016), the adjusted sample size is approximately 88 participants. This recruitment target considers potential challenges such as health issues or non-adherence, and measures like flexible scheduling, regular follow-ups, and participant engagement will be implemented to minimize dropout.

For the fMRI analyses, an effect size was selected based on prior research exploring brain activation and connectivity changes resulting from physical and cognitive interventions (Li et al., 2012; Vance et al., 2024). To achieve sufficient power, 36 participants are required. Considering a 20% dropout rate, the adjusted sample size is 44 participants. Participants who discontinue the fMRI assessments will remain included in the cognitive analysis to ensure comprehensive data utilization.

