Thus, this study aims to investigate the effects of Tai Chi combined with multisensory stimulation on cognitive function, brain structure, and sensory function in older adults with MCI. We hypothesize that this combined intervention will lead to superior improvements in both cognitive and sensory outcomes compared to single-modality interventions, potentially through the “sensory-brain-cognitive” pathway. This research aims to provide critical insights into novel non-pharmacological interventions for MCI, contributing to the development of effective and scalable prevention strategies for dementia.

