### Statistical analysis

Statistical Package for Social Sciences (SPSS) software (version 23.0) will be used for statistical analysis. An alpha level of (0.05) will be considered for all statistical tests. Two-sided *P*-values of (0.05) and (80%) power indicate statistical significance (Schulz et al., 2010). A mixed effect model will analyze the results and be employed for statistical analysis of the variance of the pretest (baseline score) and posttest (3, 6, 9 months) in the four groups. All mental, cognitive, sensory, and physical outcome measures will be used for statistical analysis. Discovery Rate (FDR) correction will be used for *post hoc* analysis.

Given the variety of cognitive and fMRI outcome measures, we will apply the False FDR to control for multiple comparisons (Genovese et al., 2002). Bonferroni correction will be used only if necessary for specific hypotheses with fewer comparisons, but FDR will be the primary approach (Alspach, 1996). An intention-to-treat (ITT) approach will be employed to handle missing data (Gupta, 2011; Little, 2024). Multiple imputations will be applied for missing cognitive data. Participants with incomplete or poor-quality fMRI data, such as those affected by motion artifacts, will be excluded from the fMRI analysis but kept in the cognitive analysis. Specific handling of missing data will depend on the outcome type.

Functional MRI (fMRI) will be utilized to evaluate neural network connectivity and the effectiveness of the intervention on brain function. Pearson correlation analysis will be conducted to assess the relationship between hippocampal subregion atrophy and the volumes of auditory and olfactory regions using structural MRI data. Similarly, Pearson or Spearman correlation coefficients will be calculated, depending on the distribution of the data, to explore the associations between fMRI-derived connectivity metrics and cognitive and sensory outcomes. These analyses aim to uncover potential neural mechanisms underlying the effects of the interventions. A sensitivity analysis will be performed by varying hypothetical dropout rates and effect sizes to assess their impact on the statistical power and required sample size (Little, 2024).

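### The 95% power for 56 participants is not shown to apply to the combined-versus-single hypothesis, and it conflicts with the 80% in the analysis section

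*Protocol article*

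**What the plan says.** The Introduction of the protocol article hypothesises that the combined intervention "will lead to superior improvements in both cognitive and sensory outcomes compared to single-modality interventions". The trial has four arms, allocated equally with 22 each (Objectives and study design).

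The Sample size section names the software but not the test: "The sample size was estimated using G*Power software, incorporating considerations for cognitive and fMRI outcomes". For cognition, it describes the effect size as "derived from previous studies evaluating Tai Chi interventions in older adults with MCI". It then states: "To achieve 95% power at a significance level, a total of 56 participants are required". An allowance of 35% for dropout takes this to about 88. The section also says that multiple comparisons were allowed for, without giving the size of the allowance.

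The Statistical analysis section sets the level: "An alpha level of (0.05) will be considered for all statistical tests". Its next sentence makes the tests two-sided and ends with "80%) power indicate statistical significance". The planned analysis is a mixed model over baseline and 3, 6 and 9 months.

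**The concern.** Two things do not fit together.

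First, an effect of Tai Chi is not the effect in question. Both the Tai Chi arm and the combined arm practise Tai Chi, so its benefit largely cancels when they are compared; what remains is the increment from adding stimulation. The comparison with stimulation alone isolates the increment from adding Tai Chi on top of stimulation, which need not equal the effect of Tai Chi in earlier trials. A power figure built on the Tai Chi effect does not carry over to either contrast without further argument, and none is printed.

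Second, the article gives two power levels, 95% and 80%, and the sentence with the second is wrong as statistics. Power is a property of the design under an assumed effect; it does not indicate that a result is significant.

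At stake is how the main comparison is read. If combined versus single is not significant, a reader who relies on the printed 95% could conclude that the combination adds nothing, although power for that comparison may be far lower.

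**Working it through.** **Inputs.** From the article: 56 evaluable, 88 recruited, 35% dropout, four equal arms of 22, alpha 0.05 two-sided, power 95% or 80%. Assumed, because the article gives no legible value: the standardised difference d between the combined arm and one single arm, and the correlation r between baseline and follow-up score.

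**The plan's own figures.** The dropout step reproduces: 56/(1 − 0.35) = 86.2, so 87, or 88 when rounded up to four equal arms. Conversely, 88 × 0.65 = 57.2. The step from effect size to 56 cannot be reproduced, since neither the effect size nor the test can be read.

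**Arm size.** 56/4 = 14 evaluable per arm; 88/4 = 22 with no dropout.

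**Power of one combined-versus-single comparison.** For a two-sample t test with n per arm, df = 2n − 2 and the noncentrality is d × √(n/2). Power is the probability that a noncentral t exceeds the 97.5% point of t.

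- n = 14, d = 0.5: df = 26, critical value 2.056, noncentrality 0.5 × √7 = 1.32, power 25%.
- n = 22, d = 0.5: df = 42, critical value 2.018, noncentrality 0.5 × √11 = 1.66, power 37%.

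Adjusting for baseline reduces the residual SD by √(1 − r²), so d is replaced by d/√(1 − r²). At d = 0.5 this is 0.577 for r = 0.5 and 0.700 for r = 0.7.

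| Per arm | Baseline adjustment | Power at d = 0.5 | Power at d = 0.8 | Power at d = 1.0 | d for 95% | d for 80% |
|---|---|---|---|---|---|---|
| 14 | none | 25% | 53% | 72% | 1.42 | 1.10 |
| 14 | r = 0.5 | 31% | 65% | 84% | 1.23 | 0.95 |
| 14 | r = 0.7 | 43% | 81% | 95% | 1.01 | 0.79 |
| 22 | none | 37% | 74% | 90% | 1.11 | 0.86 |
| 22 | r = 0.5 | 46% | 85% | 96% | 0.96 | 0.75 |
| 22 | r = 0.7 | 62% | 95% | 99% | 0.79 | 0.62 |

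If alpha is split over the two contrasts (0.025 each), 95% power at 14 per arm needs d = 1.55 unadjusted.

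**What an overall test with 95% power would imply.** Suppose, for illustration, that a four-group F test on a change score has 95% power at 14 per arm, which needs f = 0.575. The power of the two contrasts then depends on the pattern of arm means (control, each single arm, combined). These figures are from a simulation with 40,000 replicates.

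| Pattern of means | d, combined vs single | Power, each contrast | Power, both |
|---|---|---|---|
| 0, 1, 1, 2 (additive) | 0.81 | 56% | 40% |
| 0, 1, 1, 1.5 | 0.53 | 28% | 14% |
| 0, 0, 0, 1 (only the combination works) | 1.33 | 93% | 88% |
| most favourable | 1.41 | 96% | 92% |

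So 95% overall is compatible with anything from low to full power for the hypothesised contrasts.

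**The case against.** The strongest reply is that the 95% cannot be refuted. The sentence on the effect size reads "the required sample size was calculated based on an effect size of, derived from previous studies", with no value after the first phrase, and the significance level is blank in the same section. These gaps may come from text extraction and are not counted as errors. A condensed article may also leave the powered test to the full protocol. Under the most favourable pattern above, each contrast does reach about 95%. This stands: a reader might infer that the stated power is wrong, and the documents do not support that.

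A reader might also infer that the 56 came from an overall group-by-time test. That is a guess. With four groups, four visits, an assumed f of 0.25 and within-person correlation of 0.5, such a test has 97% power at 56 but needs only 52 for 95%. Two groups, f = 0.20 and four visits give exactly 56. Several tests fit, and the article does not identify one.

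Third, 25% is the bottom of a range. It assumes d = 0.5, the full 35% dropout and an unadjusted test at one visit. The planned mixed model uses baseline and repeated measures, and multiple imputation is planned for missing cognitive data. The range at d = 0.5 is 25 to 62%, and quoting only the floor would mislead. Nor does the article say that a null result would be read as no added benefit; that is a risk, not a stated intention.

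Finally, the 80% sits in a garbled sentence on significance criteria and does not claim that 88 was derived at 80%. That makes the repair largely editorial, but two unreconciled power levels remain in print. None of these replies links the 95% to the hypothesis.

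**Conclusion.** The point holds in limited form and should be fixed. The article does not show that 95% power applies to combined versus each single modality: by its own description the effect size is that of Tai Chi, not of the increment. At 14 per arm that comparison has 95% power only if the combination beats an active arm by about 1.42 SD unadjusted, or about 1.0 to 1.2 SD with an assumed baseline correlation of 0.7 to 0.5. For a difference of half an SD, power lies between 25% (14 per arm, unadjusted) and 62% (22 per arm, r = 0.7).

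All d and r values are assumptions. That the cited effect size is not an increment is inferred from the article's description of those studies. The conflict between 95% and 80%, and the misuse of power as a criterion of significance, rest on the printed text alone.

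**What to change.** 1. In the Sample size section, state the power or the detectable difference for combined versus Tai Chi and for combined versus stimulation at 24 weeks, at 14 and at 22 per arm, with the assumed SD and any baseline correlation. Name the test behind the 56.
2. Use one power figure in the Sample size and Statistical analysis sections.
3. Delete the phrase in the Statistical analysis section that links power to significance.
4. State that the two combined-versus-single contrasts will be reported as estimates with confidence intervals, so that a non-significant result can be judged by what it rules out.

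The cost is rewording in two sections and a stated power that is likely to look less favourable. No added enrolment is required for this correction, because it makes the claim match the planned size. Keeping 95% as a target for these contrasts would be a separate decision: by the normal approximation, unadjusted, it would take 104 per arm at d = 0.5 and 41 per arm at d = 0.8.

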**Secondary outcomes**	
Brain activation	Structural, and resting state functional magnetic resonance imaging (fMRI) data will be acquired using 3.0 Tesla scanner

At least five participants from each group will be randomly selected to undergo structural and resting-state functional magnetic resonance imaging (fMRI) using a 3.0 Tesla scanner. Structural MRI will allow for detailed assessment of brain anatomy, focusing on changes in brain volume, particularly in regions associated with cognitive function, such as the hippocampus and prefrontal cortex. Resting-state fMRI will assess brain connectivity and activation patterns without the need for task-based stimuli, making it ideal for observing intrinsic brain network activity (Dickerson and Sperling, 2008). The baseline scans will establish a reference point for each participant’s brain structure and function, while the post-intervention scans will reveal how the multi-domain intervention influences brain changes over time.

As part of the baseline characteristics assessment, participants will receive written feedback on their medical and health parameters, which include blood pressure (systolic and diastolic), blood glucose (fasting or random), body mass index (BMI), heart rate (HR), oxygen saturation (SpO_2_), and basic physical activity level (assessed through a questionnaire or pedometer). Participants will be advised to consult their doctor for appropriate medical management if any concerns are identified, such as high blood pressure, hyperglycemia, abnormal BMI, or low oxygen saturation.

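### The imaging sample size allows for 20% loss although the scanned participants come from a trial that expects 35%; if 44 are scanned, about 28 to 29 would be evaluable, not 36

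*Protocol article*

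**What the plan says.** All the figures are in the Sample size section of the protocol article.

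- **Cognitive outcomes:** "To achieve 95% power at a significance level, a total of 56 participants are required". The next step is "Accounting for an anticipated dropout rate of 35" per cent, after which "the adjusted sample size is approximately 88 participants".
- **fMRI:** "To achieve sufficient power, 36 participants are required", followed by "Considering a 20% dropout rate, the adjusted sample size is 44 participants".

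Three further statements determine who can be lost from imaging.

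- **Source of the scanned participants** (Baseline measurement, below Table 1): "At least five participants from each group will be randomly selected to undergo structural and resting-state functional magnetic resonance imaging (fMRI").
- **Stopping fMRI** (Sample size): "Participants who discontinue the fMRI assessments will remain included in the cognitive analysis".
- **Unusable scans** (Statistical analysis): "Participants with incomplete or poor-quality fMRI data, such as those affected by motion artifacts, will be excluded from the fMRI analysis but kept in the" analysis of cognition. The same section states multiple imputation for cognitive data only.

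The sections differ on how many are scanned. Sample size gives 44. The eligibility section has everyone who passed the criteria undergoing fMRI at baseline. Baseline measurement sets a minimum of five per group, which is 20 in all.

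**The concern.** The imaging participants are not a separate population. They are drawn at random from the randomised groups, so someone who leaves the trial before the post-intervention scan also leaves imaging. The plan then adds two losses that affect imaging alone (stopping fMRI, and exclusion for incomplete or poor-quality data) and states no method that would replace a lost scan. On that description, imaging loss would be expected to be at least as high as trial dropout. The plan instead assumes a little over half of it (20% against 35%) and does not say why.

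What is at stake is the statement that imaging has sufficient power. It rests on 36 evaluable participants, and the step from 36 to 44 is the only provision made for getting there. Brain imaging is the one secondary outcome listed in Table 1.

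**Working it through.** **Inputs (protocol article).** fMRI requirement 36, inflated to 44 at 20%. Cognitive requirement 56, inflated to 88 at 35%. Four arms, 1:1:1:1. The rates of stopping fMRI and of scan exclusion are not given. The text has no readable fMRI effect size and no numeric fMRI power, so the 36 itself cannot be re-derived.

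**1. Reproducing the plan's figures.**

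| | N/(1−d) | N×(1+d) | Stated |
|---|---|---|---|
| Cognitive | 56/0.65 = 86.2, up to 87, or 88 in equal arms | 56 × 1.35 = 75.6 | 88 |
| fMRI | 36/0.80 = 45, or 48 in equal arms | 36 × 1.20 = 43.2, up to 44 | 44 |

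The 88 fits division by the retention fraction and does not fit multiplication. The 44 fits multiplication exactly. It could also be 45 rounded down to 11 per arm. Either way, 44 × 0.80 = 35.2, which is less than one participant below 36.

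**2. The largest loss that 44 can absorb.** 1 − 36/44 = 18.2%.

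**3. Evaluable participants if 44 are scanned.** The further scan losses are assumptions, applied to those who stay in the trial.

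| Loss | Expected evaluable of 44 | Scans needed for 36 | In four equal arms |
|---|---|---|---|
| 20% (as stated) | 35.2 | 45 | 48 |
| 35% | 28.6 | 56 | 56 |
| 35%, then 5% of scans | 27.2 | 59 | 60 |
| 35%, then 10% of scans | 25.7 | 62 | 64 |
| 35%, then 20% of scans | 22.9 | 70 | 72 |

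For example, 44 × 0.65 = 28.6 and 36/0.65 = 55.4, rounded up to 56. With independent losses, the binomial chance of at least 36 evaluable out of 44 is 0.47 at 20% loss and 0.01 at 35%.

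**4. Dependence on the number scanned, at 35% loss.**

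- All 88 scanned: 88 × 0.65 = 57.2, above 36. With a further 20% scan loss: 57.2 × 0.80 = 45.8, still above 36.
- 44 scanned: 28.6.
- The floor of 20 scanned: 20 × 0.65 = 13.

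**5. Power, as illustration only.** Assume a one-way four-group F test at alpha 0.05, with the effect size back-solved from N = 36. If 36 gave 80% power, 28 to 29 give about 66% to 68%. If 36 gave 95%, they give about 87% to 88%. The plan specifies mixed-effects models and correlations, so these figures show only the direction and rough scale.

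**The case against.** The strongest objection is that the shortfall exists only if about 44 people are scanned. The eligibility section has all who qualified scanned at baseline and excludes people with MRI contraindications from the whole trial. Five per group is a floor, and 44 is a stated requirement rather than a cap. If all 88 were scanned, even a loss of 1 − 36/88 = 59% would leave 36. This stands. A reader might infer that the trial cannot deliver 36 evaluable scans, and the document does not support that inference.

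A second objection is that 20% need not contradict 35%. The 35% is said to cover non-adherence, and a non-adherent participant can still be scanned. Follow-up runs to 9 months, whereas only baseline and post-intervention scans are described, so imaging might escape later dropout. This has some force against calling the two rates a proven logical contradiction. It does not explain the 20%, because the article offers neither reason. The timing argument is also weak: Objectives and study design places the primary cognitive outcome at 24 weeks, about when a post-intervention scan would fall.

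Third, the gap at 20% is less than one participant and would not matter alone. That is correct, and it is only a side note here.

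Finally, imaging is secondary and partly exploratory of mechanism, and the cognitive sample size is unaffected. That limits the weight of the point.

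**Conclusion.** The point holds in a limited form. The plan allows for 20% loss in a random subset of a trial that expects 35%, adds imaging-only losses, and gives no reason for the lower rate. If 44 are scanned and the trial's rate applies to them, 28 to 29 are expected to be evaluable, 7 to 8 fewer than the 36 required (36 − 28.6 = 7.4), before any scan-quality loss. The one-participant gap at 20%, and the apparent use of two inflation formulas in adjacent paragraphs, are secondary.

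The conclusion assumes that trial dropout removes the follow-up scan and that about 44 are scanned. A reader might go further and conclude that the imaging analysis is underpowered by a known amount. The document does not support that, because it gives no readable effect size or numeric power for fMRI and does not settle how many are scanned.

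Severity is minor to moderate: it concerns a stated figure for a secondary outcome and is cheap to correct.

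**What to change.** 1. Use one attrition assumption for imaging, namely trial dropout plus a stated allowance for stopped or unusable scans, and inflate by N/(1−d) as was done for the cognitive outcomes. If a rate below 35% is intended, give the reason.
2. Reconcile the number scanned across Sample size (44), the eligibility section (all) and Baseline measurement (at least 20).
3. Then take one of two courses:
   - keep 44, and state that about 28 or fewer are expected to be evaluable, with the power that this gives; or
   - scan at least 56 of the 88 already planned (14 per arm), or 60 to 72 in equal arms if a further 5% to 20% of scans are assumed lost.

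Changing 44 to 45 is not enough: it keeps the unexplained 20% and does not divide into four equal arms.

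No extra enrolment is needed. The cost is a less favourable imaging power statement or 12 or more additional scans (56 − 44 = 12). If baseline scanning is already complete, only the restatement is available.

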### Criteria for participants’ inclusion and exclusion

The study started on 1 May 2024, and patients with MCI who lived in Shanghai and Suzhou communities were recruited. First, a geriatrician checked the following initial eligibility criteria: age 60 years or older, diagnosis of dementia reported in the patient’s medical file by the dementia diagnosis team or a medical specialist, and absence of serious health problems that could preclude safe participation (Bossers et al., 2015). Next, a trained Human Movement Sciences (HMS) research assistant tested the patients for the following additional inclusion criteria: Mini-Mental State Exam (MMSE) score of at least 19 to no more than 23 and the ability to perform the timed up-and-go test (Podsiadlo and Richardson, 2015), ADL score above 26 (Fuentes et al., 2020). Those who passed these six criteria completed a neuropsychological test and fMRI at baseline (time zero, T0) administered by an experienced and trained research assistant.

Exclusion criteria include participants with severe medical conditions (e.g., advanced cardiovascular disease, uncontrolled diabetes, cancer) or neurodegenerative disorders (e.g., Huntington’s disease, Parkinson’s disease) to ensure the study focuses on individuals with MCI. Participants with exercise limitations (e.g., recent surgery, joint issues), those unable to undergo MRI due to contraindications (e.g., pacemakers, metal implants, claustrophobia), or those with a history of excessive alcohol use (> 14 drinks/week) or smoking (> 10 cigarettes/day) will also be excluded to minimize confounding factors.

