**Methods and analysis:**

The TaiChi-MSS (Tai Chi and Multisensory Stimulation for Cognitive Function) study is a multi-center, randomized controlled trial (RCT) conducted in Suzhou and Shanghai, enrolling 88 participants aged 60 years or older with MCI. Participants will be randomly assigned to one of four groups: Tai Chi, multisensory stimulation, Tai Chi combined with multisensory stimulation or control. The intervention will last 6 months, with follow-up assessments at 3, 6, and 9 months. Primary outcomes include cognitive and sensory assessments, assessed using the Montreal Cognitive Assessment (MoCA), Mini-Mental State Examination (MMSE), domain-specific cognitive tests, Pure Tone Audiometry (PTA), and Sniffin’ Sticks Odor Identification Test. Secondary outcomes involve brain activation, measured through functional Magnetic Resonance Imaging (fMRI) scans. fMRI will be used to assess brain structure and connectivity changes, focusing on neuroplasticity. Data will be analyzed using mixed-effects models. The False Discovery Rate (FDR) will be the correction method for multiple comparisons to control for the expected proportion of false positives.

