## Introduction

China is one of the greatest countries that undergoes worldwide and rapid demographic progress, with the proportion of people aged 65 reaching 12.6% of the total population. In urban areas such as Shanghai, this proportion has already reached 21.8%, making it a “super-aged” city (Mitchell, 2015). This demographic shift presents a significant challenge, particularly with regard to the cognitive decline associated with aging. Alzheimer’s disease (AD), the most prevalent form of dementia, is typified by progressive cognitive decline, loss of functional autonomy, and considerable societal and economic burdens (Jack et al., 2024).

The findings of recent research indicate that Alzheimer’s disease commences its development approximately 10–15 years prior to the point at which a clinical diagnosis is made. This evidence underscores the vital importance of early intervention (Amieva et al., 2008; Bateman et al., 2012). Mild cognitive impairment (MCI) has become a key focus for preventive strategies, as it represents a transitional stage between normal cognitive aging and dementia (Jin et al., 2023; Rozzini et al., 2007). MCI is characterized by subjective cognitive complaints and measurable cognitive impairment, though functional abilities remain largely intact and do not yet meet the criteria for dementia (Anand and Schoo, 2024). In China, approximately 14.71% of the elderly population is estimated to be affected by MCI, underscoring the urgent need for effective intervention strategies (Xue et al., 2018). Especially at early preclinical stages such as early and stable MCIs (Zhou, 2021), these advancements hold significant promise for improving early diagnosis and intervention strategies.

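### A recorded diagnosis of dementia is printed as an inclusion criterion in a trial whose stated population, mild cognitive impairment, excludes dementia by the article's own definition

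*Protocol article*

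**What the plan says.** **Stated population.** The Abstract describes a trial "enrolling 88 participants aged 60 years or older with MCI". The Introduction gives the aim as studying effects on "cognitive function, brain structure, and sensory function in older adults with MCI". It places MCI before dementia ("it represents a transitional stage between normal cognitive aging and dementia") and says that in MCI "functional abilities remain largely intact and do not yet meet the criteria for dementia".

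**Eligibility.** The section on inclusion and exclusion criteria opens by saying that patients with MCI living in Shanghai and Suzhou communities were recruited. It then describes screening in two steps:

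- A geriatrician's check, given as: "First, a geriatrician checked the following initial eligibility criteria: age 60 years or older, diagnosis of dementia reported in the" patient's medical file. The diagnosis is to come from a dementia diagnosis team or a medical specialist. The last item in this step is the absence of serious health problems.
- A research assistant's check of MMSE, ability to do the timed up-and-go test, and an ADL score.

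Those who passed all six criteria went on to baseline testing. The exclusion paragraph lists severe medical conditions and neurodegenerative disorders, with the stated purpose "to ensure the study focuses on individuals with MCI". It does not name dementia.

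**The concern.** The eligibility list decides whom the results describe. Here one sentence says that people with MCI were recruited, and the next requires a diagnosis that the article's definition of MCI rules out. A screener following the list as printed would turn away a person with MCI and no dementia, and would accept a person with dementia who met the other items.

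The estimated effects would then belong to a population that the trial does not claim to study. The Discussion presents the trial as extending work done mostly in Alzheimer's disease to people with MCI, and that contribution would be lost. The Sample size section also takes its effect size from work said to be in older adults with MCI, so the planning basis would no longer match the people admitted.

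**Working it through.** No power or sample-size formula bears on this point. The check is a count of the criteria and a comparison of the sections.

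**1. Reproduce the stated count of six.**

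- Geriatrician: (1) age 60 or older; (2) recorded diagnosis of dementia; (3) no serious health problems.
- Research assistant: (4) MMSE 19 to 23; (5) able to do the timed up-and-go test; (6) ADL above 26.

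3 + 3 = 6, as stated. The diagnosis item is therefore a criterion to be passed. Without it the count is 5.

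**2. Can the sentence be read as requiring no dementia?** No. The word for absence comes after the diagnosis item and governs only the serious health problems.

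**3. Set the criterion against the stated population**, for a person who meets the other five criteria and no exclusion:

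| Person | Passes the printed list? | In the stated MCI population? |
|---|---|---|
| MCI as the Introduction defines it, no dementia diagnosis | No | Yes |
| Recorded, correct diagnosis of dementia | Yes | No |
| Both at once | Not possible under the Introduction's definition | Not possible |

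The people admitted by the list and the people in the stated population do not overlap.

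**4. Look for a correction elsewhere.** None of the six criteria requires an MCI diagnosis. The exclusion paragraph does not list dementia. The Abstract, the Introduction and the opening of the eligibility section name MCI but leave the criterion untouched.

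**5. Does the planned number depend on this?** No. From the Sample size section, 56 / (1 − 0.35) = 86.15, which rounds up to 87, and to 88 for four equal arms of 22. The total of 88 is reproduced whichever diagnosis is meant. What could fail to carry over is the effect size behind the 56, and only if the printed criterion was applied.

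**The case against.** The strongest reply is that this is a drafting slip. The recruitment sentence, the purpose given for the exclusions, the Abstract and the aim all say MCI, and the criteria carry an outside citation from which the wording may have been taken. The count of six does not settle the matter: putting MCI in place of dementia in that one item also gives six. The count shows that a diagnosis was required, not that dementia was the intended word. The full protocol is not shown and may word the item correctly.

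All of this stands as explanation, but it does not remove the contradiction. An article may leave detail to the full protocol, but here it prints a specific criterion that conflicts with its own definition.

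Four stronger readings are tempting and are not supported:

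- *That the wrong people have been enrolled.* The article gives a start date but does not say who was enrolled or which wording the sites used.
- *That the exclusion of neurodegenerative disorders leaves nobody eligible.* The examples given are Huntington's and Parkinson's disease. Whether dementia was meant to fall under that exclusion is conjecture. The sound route to an empty set is requiring MCI and dementia together.
- *That the MMSE window ("score of at least 19 to no more than 23") and the ADL cut-off are also wrong for MCI.* The article ties neither figure to MCI or to dementia, and its definition of MCI gives no score, so this cannot be judged from the document.
- *That the sample size is invalid.* The effect size does not appear in the text. The study cited for it is also cited for the eligibility list, and is not at hand. A mismatch follows only if the printed criterion was applied.

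**Conclusion.** The contradiction is real, and the text as printed must be fixed. The eligibility section conflicts with its own opening sentence, with the Abstract and with the Introduction's definition and aim. Read literally, it admits only people with recorded dementia, and no one can satisfy both that criterion and the stated population, so the MCI question could not be answered.

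The wording bears on eligibility for all 88 planned participants. Its practical effect may be anything from none, if the sites screened for MCI, to the whole sample, if they followed the printed list. The article does not allow a choice between these.

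The conclusion rests on two assumptions: that the Introduction's definition of MCI is the one the trial uses, and that a dementia diagnosis recorded by a specialist means the criteria for dementia were met.

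**What to change.** Reconcile the eligibility section with the Abstract and Introduction in one of two ways:

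- If MCI is the population, replace the dementia item with a documented diagnosis of MCI that fits the Introduction's definition, and list a dementia diagnosis as an exclusion.
- If people with dementia are intended, change the stated population, the aim and the basis of the sample size.

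If the full protocol already has the right wording, a correction to the article is enough. If it carries the same sentence, a protocol amendment is needed.

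Recruitment began on 1 May 2024, so the sponsor should also confirm in writing which criterion the sites applied. If the printed wording was used, check the files of those enrolled and report how many carried a dementia diagnosis.

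The cost is one correction or amendment and a query to the sites, plus a file check of at most 88 participants if the printed wording was used. The first option leaves the planned number unchanged. The second would require it to be justified again.
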